6.3 Missing Data

6.3.1 Direct Likelihood

In the event that some C-peptide AUC values are not available at 12 months, then the primary analysis will use the method of direct likelihood to incorporate information from previous measurements to calculate the maximum likelihood estimate at 12 months.

It is worth noting that all statistical methods for handling missing data rely on untestable assumptions and there is no one correct way to handle missing data. Our goal is to minimize the amount of missing data so that the results will not be sensitive to which statistical method is used.

6.3.2 Sensitivity Analyses

Sensitivity analyses will also be performed to assess the effects of the statistical method for missing data on the primary outcome. Analyses will be performed using the following two methods:

- Available cases only
- Rubin’s multiple imputation based on previous C-peptide AUC measurements at baseline or 6 months

7 Analysis of the Secondary Endpoints

The following table displays the times at which each type of outcome metric listed in Section 4 is measured:

| Outcome Metric                    | Baseline | 3 Months | 6 Months | 9 Months | 12 Months | 15 Months | 18 Months | 21 Months | 24 Months |
|-----------------------------------|----------|----------|----------|----------|-----------|-----------|-----------|-----------|-----------|
| C-Peptide AUC                     | X        |          | X        |          | X*        |           |           |           | X         |
| Fasting C-peptide/fasting glucose | X        |          | X        |          | X         |           |           |           | X         |
| HbA1c Metrics                     | X        | X        | X        | X        | X         | X         | X         | X         | X         |
| CGM Metrics                       | X        | X        | X        | X        | X         | X         | X         | X         | X         |
| Insulin Metrics                   | X        | X        | X        | X        | X         | X         | X         | X         | X         |
| Height/Weight (to calculate BMI)  | X        |          | X        |          | X         |           |           |           | X         |
| Blood Pressure                    | X        |          | X        |          | X         |           |           |           | X         |
| Lipid Profile Metrics             | X        |          |          |          | X         |           |           |           | X         |

\* Primary outcome

In the table above, each metric is collected at the time points marked with an “X”.

Additionally, the following table displays the times at which each type of outcome metric is measured during the extension phase:

| Outcome Metric                    | 27 Months | 30 Months | 33 Months | 36 Months | 39 Months | 42 Months | 45 Months | 48 Months |
|-----------------------------------|-----------|-----------|-----------|-----------|-----------|-----------|-----------|-----------|
| C-Peptide                         |           |           |           | X         |           |           |           | X         |
| Fasting C-peptide/fasting glucose |           |           |           | X         |           |           |           | X         |
| Fasting Blood Glucose             |           |           |           | X         |           |           |           | X         |
| HbA1c Metrics                     | X         | X         | X         | X         | X         | X         | X         | X         |
| CGM Metrics                       |           |           |           | X         |           |           |           | X         |
| Insulin Metrics                   | X         | X         | X         | X         | X         | X         | X         | X         |
| Height/Weight (to calculate BMI)  |           |           |           | X         |           |           |           | X         |

F:\user\Diabetes Studies\JDRFAPP\Protocols\APCam Newly Diagnosed - CLOuD\Statistics\Electronic Binder\4. SAP\CLOuD SAP V2.0 4-4-19.docx

|                       |  |  |  |   |  |  |  |   |
|-----------------------|--|--|--|---|--|--|--|---|
| Blood Pressure        |  |  |  |   |  |  |  |   |
| Lipid Profile Metrics |  |  |  | X |  |  |  | X |

227

228 As shown above, blood pressure will not be measured during the extension phase. There also  
229 will not be any MMTTs occurring during the extension phase. Only C-peptide and fasting blood  
230 glucose will be measured during the extension phase. Values for those two metrics will be  
231 compared between treatment groups at 36 and 48 months as described below.

232 Per the protocol, lipid profile metrics are not considered to be secondary endpoints during the  
233 extension phase, so they will not be compared between treatment groups at 36 and 48 months.  
234 Instead, only summary statistics will be reported at those time points.

235 **7.1 Out Of Window Visits**

236 As shown in the table above, each of the following variables are collected at study follow-up  
237 visits:

- 238     • C-peptide  
239     • HbA1c  
240     • Height and weight to calculate BMI  
241     • Blood pressure  
242     • Lipids

243 For each of these metrics, analysis windows will be as follows:

244

| Visit     | Window            |
|-----------|-------------------|
| 3 months  | Days 60 to 120    |
| 6 months  | Days 150 to 210   |
| 9 months  | Days 240 to 299   |
| 12 months | Days 300 to 420   |
| 15 months | Days 421 to 480   |
| 18 months | Days 510 to 570   |
| 21 months | Days 600 to 660   |
| 24 months | Days 661 to 780   |
| 27 months | Days 781 to 840   |
| 30 months | Days 870 to 930   |
| 33 months | Days 960 to 1020  |
| 36 months | Days 1021 to 1140 |
| 39 months | Days 1141 to 1200 |
| 42 months | Days 1230 to 1290 |
| 45 months | Days 1320 to 1380 |
| 48 months | Days 1381 to 1500 |

245

246 These windows do not apply to the CGM metrics, which are calculated as described above.

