## 3 Sample Size

Assuming a mean area under the meal stimulated C-peptide curve of 0.37 pmol/ml for the control group based on the lower 90% confidence limit from previous data, a 50% increase in the intervention group gives  $0.37 \times 1.50 = 0.555$  pmol/ml. After a  $\ln(x+1)$  transformation, the mean values in the control and treatment groups are 0.315 and 0.441, respectively, giving a treatment effect of  $0.441 - 0.315 = 0.126$ . The treatment effect of 0.126 with a standard deviation of 0.18 requires 44 subjects per group at 90% power for a two sided-test at the 0.05 level. Allowing for 10% loss to follow up means we would need a total of 96 randomized participants (48 per group).

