## 5 Description of Statistical Methods

### 5.1 General Approach

This is an open-label, multi-center, single-period, randomized, parallel group design study of participants aged 10 to <17 years. It is expected that a total of up to 190 subjects will be recruited within ten working days of diagnosis of type 1 diabetes (T1D) through pediatric diabetes centers in the UK. Half of the participants will be treated by conventional multiple daily injection therapy (MDI) and the other half by closed loop insulin delivery system (CL). Initiation of treatment arm occurs at study visit 5 and will last 24 months. Additionally, subjects will have the option to participate in an extension phase that will go until 48 months.

The study includes up to 14 visits and 1 telephone/email contact for subjects completing the study. For subjects completing the extension phase, it will include an additional 3 visits and 6 contacts. After initiation of the treatment arm, visits will be conducted every 3 months in both arms during the main study and the optional extension phase. Beta-cell function will be assessed by serial measurement of C-peptide in response to a standardized MMTT. MMTTs will be conducted at baseline, 6, 12, and 24 months post diagnosis.

All analyses will compare the CL arm with the MDI arm and will follow the intention-to-treat principle with each participant analyzed according to the treatment assigned by randomization regardless of actual CL utilization. All randomized participants who have at least one CGM reading during the 24 month study period will be included in the secondary analyses of CGM metrics. For secondary analyses of CGM metrics after 24 months, only subjects with at least one reading occurring during the extension phase (i.e. after the date of the 24 month visit) will be included. The primary analysis will include all randomized participants.

All covariates obtained on a continuous scale will be entered into the models as continuous variables, unless it is determined that a variable does not have a linear relationship with the outcome. In such a case, categorization and/or transformation will be explored. All p-values will be two-sided.

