## 14.7 Sample size and power calculations

The primary analysis will compare the difference between groups in the levels of the 2-hour AUC-mean using the  $\ln(\text{mean C-peptide}+1)$ . The residual standard deviation of the  $\ln(x+1)$  transformed C-peptide AUC analysis of covariance is referred to by TrialNet (Lachin 2011) as the root mean squared error (RMSE). The back-transform,  $\exp(y) - 1$ , of the mean of the transformed values is referred to by TrialNet as the geometric-like mean. In the DirecNet/TrialNet new onset studies (Lachin 2011), the point estimate for RMSE was 0.18 (transformed scale) and was used in the power calculations. As in the TrialNet sample size calculations, a 50% improvement was assumed in the geometric-like mean C-peptide AUC. The sample size depends on the geometric-like mean value in the control group. The original TrialNet sample size calculations assumed a value of 0.37 pmol/ml for the control group based on the lower 90% confidence limit from previous data (Lachin 2011). The present power calculation applied the same value. A 50% increase in the intervention group of the geometric-like mean C-peptide AUC gives  $0.37 \times 1.50 = 0.555 \text{ pmol/ml}$ . After  $\ln(x+1)$  transformation, the mean values in the control and treatment groups are 0.315 and 0.441 (transformed scale), respectively, the treatment effect is  $0.441 - 0.315 = 0.126$ . The treatment effect of 0.126 with a standard deviation of 0.18 requires 44 subjects per group at 90% power for a two sided-test at the 0.05 level. Allowing for 10% loss to follow up means we would need a total of 96 randomised participants (48 per group).

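### No planned analysis of the primary outcome deliberately departs from missing-at-random, so an overstatement of up to about 11% at the planned 10% loss could not be diagnosed

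*Combined protocol and SAP*

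**What the plan says.** SAP 5.1 sets an intention-to-treat question: participants are analysed by assigned arm "regardless of actual CL utilization", and the primary analysis takes in everyone randomised.

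For missing 12-month values, SAP 6.3.1 states that "the primary analysis will use the method of direct likelihood to incorporate information from previous measurements". The same section concedes that every missing-data method depends on assumptions that cannot be tested, and it relies on keeping missing data rare.

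SAP 6.3.2 lists two sensitivity analyses, meant to show how much the missing-data method affects the primary outcome:

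- "Available cases only"
- "multiple imputation based on previous C-peptide AUC measurements at baseline or 6 months"

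Neither the SAP nor the protocol contains a delta-adjusted, tipping-point, reference-based or other not-at-random analysis.

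The protocol does plan to limit missing data. The synopsis (withdrawal criteria) and protocol 9.15 ask sites to keep following participants who stop the intervention. The specific invitation to a mixed meal tolerance test (MMTT) after withdrawal in 9.15 is narrower. It covers withdrawal reasons 5 to 11 and is set at the end of the planned intervention, not expressly at month 12. Reasons 2 and 3 (failure during post-randomisation training) are outside it.

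**The concern.** Direct likelihood gives a closed-loop participant with no 12-month value the outcome expected of observed closed-loop participants with the same history. For an intention-to-treat effect that is right only if those with missing values did about as well. There are reasons to doubt it for some of them. The study supplies the closed-loop components (protocol 9.21). A participant who does not show competency with the system cannot enter the home phase (9.7.1), and might have a baseline MMTT only and almost no exposure to closed loop.

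Sensitivity analyses exist to show what happens when such an assumption fails. Available cases makes the same assumption or a stronger one, because it ignores the 6-month value. The imputation either repeats the primary assumption or changes the answer for an unrelated reason, depending on whether arm is in the model. What is at stake is the size of the treatment effect, and whether the report can say that it is robust to missing data.

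**Working it through.** **The plan's own figure.** SAP 3 and protocol 14.7 use ln(1.37) = 0.315 and ln(1.555) = 0.441, a difference of 0.126, and state: "The treatment effect of 0.126 with a standard deviation of 0.18 requires 44 subjects per group". The normal formula gives 2 × [0.18 × (1.960 + 1.282) / 0.126]² = 42.9, so 43 per group. The noncentral t gives 44 (power 0.901 at 44, 0.894 at 43). The stated 44 is reproduced. Of 48 randomised per arm, 10% loss leaves 48 × 0.9 = 43.2.

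**Size of the possible overstatement.** Let d be the share of the closed-loop arm with a missing 12-month value and r the share of the benefit they keep. The documents give d = 10% as the planning value; r is an assumption.

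- Estimate under missing-at-random: 0.126
- True intention-to-treat effect: 0.126 × [(1 − d) + d × r]

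| d | r | True effect | Overstatement |
|---|---|---|---|
| 10% | 0 | 0.126 × 0.90 = 0.1134 | 0.126/0.1134 − 1 = 11.1% |
| 10% | 0.5 | 0.126 × 0.95 = 0.1197 | 5.3% |
| 10% | 1 | 0.126 | 0% |
| 5% | 0 | 0.126 × 0.95 = 0.1197 | 5.3% |
| 20% | 0 | 0.126 × 0.80 = 0.1008 | 25.0% |

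An overstatement of 10% needs d = 1 − 1/1.10 = 9.1% with nothing kept. At 43 per group, normal-formula power for 0.1134 is 0.83 instead of 0.90.

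**Imputation without arm, no 6-month value, 10% loss in each arm.** The pooled mean of the observed values is (0.441 + 0.315)/2 = 0.378. The imputed arm means are 0.9 × 0.441 + 0.1 × 0.378 = 0.4347 and 0.9 × 0.315 + 0.1 × 0.378 = 0.3213, a difference of 0.1134. Only observed values enter this sum. The answer is therefore 0.1134 both when the lost participants have no benefit (truth 0.1134) and when missing-at-random holds (truth 0.126).

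**Large-sample simulation**, 400,000 per arm, 10% loss in each arm. Assumptions not in the documents: 6-month effect 0.063, residual correlation between 6 and 12 months 0.7. Direct likelihood was computed as imputation with arm in the model, which is equivalent in large samples. Monte Carlo error is about 0.18 × √(2/400,000) = 0.0004.

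| Lost closed-loop participants | Truth | Direct likelihood | Available cases | Imputation without arm |
|---|---|---|---|---|
| No 6-month value, none kept | 0.1134 | 0.1262 | 0.1262 | 0.1136 |
| 6-month value with benefit, none kept at 12 | 0.1133 | 0.1258 | 0.1259 | 0.1189 |
| 6-month value already without benefit, none kept at 12 | 0.1141 | 0.1214 | 0.1267 | 0.1142 |
| 6-month value with benefit, all kept | 0.1265 | 0.1266 | 0.1266 | 0.1195 |

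In the second row the primary result is biased by 11%, and imputation without arm differs from it by 0.1258 − 0.1189 = 0.0069. In the last row there is no bias, and the difference is 0.1266 − 0.1195 = 0.0071. A reader could not tell the two cases apart.

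**How far a tipping point must run.** The standard error at 43 per group is 0.18 × √(2/43) = 0.0388. Lowering the imputed closed-loop values by 0.126 gives 0.126 − 0.10 × 0.126 = 0.1134, which is still 0.1134/0.0388 = 2.9 standard errors from zero. Reaching 1.96 × 0.0388 = 0.0761 would need a shift of (0.126 − 0.0761)/0.10, about 0.50. That exceeds the planned closed-loop mean of 0.441 on a scale that cannot fall below zero. This is approximate, since it ignores the extra variance from imputation; a smaller observed effect would tip sooner.

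**The case against.** Five points on the other side have weight.

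- **Silence about arm.** A reader might infer that the imputation leaves treatment arm out. The text does not say so: one line names the earlier C-peptide values and neither includes nor excludes anything else. The direct likelihood sentence is just as short. This stands. What remains is that arm must be in a likelihood that estimates the difference between arms, whereas an imputation model is a separate model whose contents have to be stated.
- **Detection.** A reader might also infer that a bias would leave no trace. If arm is left out, imputation moves towards the truth in the biased scenarios, sometimes all the way. This stands too, but it moves just as far when there is nothing to correct.
- **Stopping closed loop is not missing data.** Participants who stop but attend the 12-month MMTT are observed and create no bias of this kind, and the protocol tries to keep them. Values may also be missing because the test fell outside days 300 to 420 (SAP 6.1) or had too few samples (SAP 4.1). In people still on closed loop there is then no reason to assume a lost benefit. Both points stand and reduce the likely size.
- **Worst case.** At planned loss, 11% requires that nothing is kept. It is about 6% where the 6-month value already shows the loss. Larger figures need more loss in the closed-loop arm than planned, which the documents do not project.
- **No false positive.** Under this mechanism the bias is d × (1 − r) × effect, so it is zero when the true effect is zero. The shift at planned loss, 0.0126, is about a third of a standard error.

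**Conclusion.** The point holds as a gap in the sensitivity analyses, not as a fault in the primary method. Direct likelihood is a reasonable primary choice. The two listed checks cannot show whether its assumption matters: available cases shares or strengthens that assumption, and the imputation is either redundant (arm in) or non-diagnostic (arm out).

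At the planned 10% loss the effect could be overstated by up to about 11% (0.126 against about 0.113) if closed-loop participants with missing values keep none of the benefit. It is about 5% if half is kept or loss is 5%, and zero if all is kept. These figures rest on the planned effect and loss and on an assumed share of benefit kept, which the documents do not give. The documents do not support saying that the imputation omits arm, that any bias would pass unseen, or that an overstatement of 10% or more is to be expected. This is a cheap improvement to make before analysis.

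**What to change.** Keep direct likelihood as the primary analysis. In SAP 6.3.2:

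1. State that the imputation model includes treatment arm and the covariates of the primary model (SAP 6.2). This clarifies the analysis; it does not by itself test the assumption.
2. Add at least one not-at-random analysis of log(C-peptide AUC+1) at 12 months:
   - reference-based imputation, drawing missing closed-loop values from the MDI arm given baseline and any 6-month value; and/or
   - a delta-adjusted tipping point that lowers imputed closed-loop values until significance is lost or the values become implausible. It should not stop at −0.126, because at the planned loss and effect significance would survive that shift. The significance level must be stated, since SAP 6.2 gives 5% and SAP 13 gives 0.04.

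The cost is SAP wording and a little programming, with no new data, participants or procedures. The downside is that the sensitivity estimates may be slightly less favourable to closed loop.

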## 7.2 Baseline BMI Standard Deviation Scores and Blood Pressure

### Calculation

Baseline BMI will be calculated using height and weight measurements taken at the recruitment visit.

Baseline systolic and diastolic blood pressure measurements will be taken to be the values recorded at the baseline MMTT (if both are known) because it is closer to randomization than the recruitment visit. If either of these values are missing at the baseline MMTT, then the values obtained during the recruitment visit will be used instead (if both are known). If at least one of these values is missing at the baseline MMTT and the recruitment visit, then the values may be taken from different visits. The value at the baseline MMTT will be used if it is known. Otherwise, the value at recruitment will be used instead.

### Inclusion in Statistical Models

These baseline values will be included in the models as covariates when comparing outcomes 18)-20) listed above between treatment arms.

## 7.3 Regression Modeling

At 12 months post diagnosis, a longitudinal analysis will be conducted for the primary outcome and each continuous secondary outcome using a linear mixed model with a random intercept and slope. For binary outcomes, a repeated measures logistic regression model will be used. All data collected up to and including the 12 month visit will be used to fit the models. The models will account for repeated measures coming from the same subject using an unstructured covariance matrix. They will adjust for baseline value, gender, presence or absence of DKA at diagnosis, and age as fixed effects, in addition to site as a random effect. If necessary, they may also adjust for HbA1c levels, BMI z-score, or race/ethnicity to assess for the presence of confounding. Residual values will be examined for an approximate normal distribution. If values are highly skewed, then a transformation or non-parametric methods will be used instead.

Using these longitudinal models, one treatment arm comparison will be performed specifically at 12 months for each metric and another treatment arm comparison will be performed combining data over all follow-up visits. The latter will be calculated using a linear contrast giving equal weight to each follow-up visit.

A composite analysis will not be performed for the lipid profile metrics, because they are not collected at any time points between the baseline visit and the 12 month visit (see table above).

An analogous longitudinal model will also be run at 24 months for each outcome metric, and at 36 and 48 months for subjects who participated in the extension phase.

In addition to the longitudinal models, boxplots will be used to display the distributions of the primary and secondary outcomes over time. If the longitudinal model produces a significant composite p-value for a particular outcome, then the boxplots will be used to explore the time at which the outcome began to differ between treatment arms.

#### 7.4 Analysis of C-Peptide AUC at 6 Months

If the primary outcome is declared significant, then it will also be compared between treatment groups at six months using the same approach described above.

#### 7.5 Missing Data

In the event that a particular outcome metric is unavailable at 12, 24, 36, or 48 months but data is available at previous time points, it will be estimated using the method of direct likelihood described in section 6.3.1. This method will be applied to all applicable secondary outcomes.

In the HbA1c analyses, the primary outcome will be venous HbA1c, and capillary HbA1c will be treated as an auxiliary variable.

Missing CGM data will not be imputed in this study.

